# Sedentariness and Back Health in Western Cape Primary School Students: Protocol for a Pragmatic Stepped-Wedge Feasibility Randomized Controlled Trial

**DOI:** 10.2196/18522

**Published:** 2020-11-30

**Keywords:** sitting, standing, postural dynamism, sit-stand desks, classroom, school, sedentary, children

## Abstract

**Background:**

Despite growing evidence of deleterious health outcomes associated with sedentary behavior, prolonged static sitting in classrooms remains ubiquitous in primary schools. Sedentary behavior is associated with the development of cardio-metabolic conditions and poor back health. Preventative strategies to reduce sedentary behavior and its negative health effects may be required in a resource-constrained environment such as South Africa.

**Objective:**

The primary objective of this study is to assess the feasibility of conducting a full trial to evaluate the effects of a multifaceted intervention comprising novel multifunctional classroom furniture and a video-based curriculum versus usual care on sedentary behavior among students aged 10-11 years in primary schools. The secondary objective is to assess the preliminary effects of the intervention on sedentary behavior and postural dynamism.

**Methods:**

Eighty grade 5 or 6 students, aged 10 and 11 years, in mixed-gender schools within the Western Cape metropolitan urban area in Cape Town, South Africa are eligible to participate in this pilot cluster stepped-wedge trial design with classroom as the unit of randomization. Data will be collected at the schools. The intervention will comprise multifunctional classroom furniture that allows for sitting and standing as well as a video-based curriculum on sedentary behavior. Usual practice is the absence of the intervention. The primary outcomes assessed will be (1) adherence to the intervention and (2) project pragmatics. The secondary outcomes will be (1) sedentariness measured using activPAL3 microsensors and (2) postural dynamism measured using Noraxon Myomotion inertial measurement units. We randomized the school to the first or second start of the intervention. This is an open-label trial and therefore blinding will not be possible for any group. Descriptive analysis of the feasibility and physiological outcomes will be presented. We will report the preliminary estimates of the effects of the intervention on sedentariness and postural dynamism using the mean difference and 95% CI.

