## Methods

### Study Design

This study protocol, designed according to the CONSORT (Consolidated Standards of Reporting Trials) statement for feasibility trials [25], has a stratified, closed cohort, two-cluster stepped-wedge design with a pragmatic approach. The stepped-wedge design offers an ideal structure that allows for a robust evaluation of an intervention within the bounds of logistical constraints [27]. In addition, this study design allows both clusters to be exposed to the intervention with consideration of the unique context of each cluster.

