### Participants

Two primary schools were recruited for participation in the study. Participant classrooms (children aged 10-11 years) will be the unit of randomization and both classrooms (clusters) will be exposed to the intervention but will serve as their own control. All participants in each cluster will be exposed to the intervention from which a sample will be selected to provide baseline and follow-up measurements, and qualitative interviewing. Measurements for each selected participant will be taken at baseline, prior to the onset of intervention implementation, and followed up at the end of the trial period. Baseline measurements and implementation of the intervention in classroom 2 will follow those of classroom 1. This study was granted ethical approval by Stellenbosch University Health Research Ethics Committee (reference number: S17/08/130).

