### Trial Design

This is a school-based, pilot cluster stepped-wedge feasibility trial. Individual students in grade 5 or 6 (10-11 years old) will be the unit of analysis with the classroom as the unit of randomization. Quintiles are socioeconomic categorizations of schools in South Africa that determine the state funding of the school, which is based on income levels, dependency ratios, and literacy rates in the area [28]. Although there will be no need to stratify the randomization of the clusters in this trial as there are only two participant classrooms, it is proposed that stratification by school quintile should be carried out during a future full trial. Baseline physiological data will be measured prior to the start of the intervention. Interviews with teachers and focus group discussions will be conducted after the intervention to assess the feasibility of the study. Figure 1 shows the proposed study design, and Multimedia Appendix 1 provides a SPIRIT diagram [29] for the design and timescales of the feasibility study.

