### Data Analysis

#### Statistical Analysis

As per the CONSORT statement [25], feasibility outcomes will be described descriptively and narratively. Descriptive statistics will be used to report the clinical endpoints related to the feasibility outcomes. The number of participant classrooms and students, the number of children that remain in the study, and how many children use the school furniture throughout the study will be summarized. Owing to the small sample size, inferential statistics will most likely not be applicable. Study acceptability data will be presented per cluster as well as for the whole sample.

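### The promised 95% CI for the intervention effect is not reconciled with the analysis section, and a student-level interval from two classrooms would not be a valid one

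*Protocol article*

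**What the plan says.** The abstract (Methods) commits to effect estimates with intervals: "We will report the preliminary estimates of the effects of the intervention on sedentariness and postural dynamism using the mean difference and 95% CI". The Statistical Analysis section names no effect estimate and no interval, and says: "Owing to the small sample size, inferential statistics will most likely not be applicable".

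On units, Trial Design states: "Individual students in grade 5 or 6 (10-11 years old) will be the unit of analysis with the classroom as the unit of randomization". On structure, Study Design says that the trial "has a stratified, closed cohort, two-cluster stepped-wedge design with a pragmatic approach". The abstract adds "We randomized the school to the first or second start of the intervention", and Participants adds "Baseline measurements and implementation of the intervention in classroom 2 will follow those of classroom 1". Each start time therefore has one classroom. Sample Size makes one of them fee-paying and the other nonfee-paying.

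On timing, Participants describes two occasions per sampled student: one before the intervention begins and one when the trial closes. The same section says that each classroom acts as its own control. Sample Size plans physiological data from 20 students per cluster. Results reports baseline data from 10 per class at submission. The article gives no ICC, no SD and no allowance for time.

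**The concern.** A 95% CI around an intervention effect is inference. One part of the article promises it and another expects it not to apply, so an analyst cannot tell which statement governs.

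The reason given, small sample size, points at the number of students. The binding limit is the number of classrooms. All students in a class share a teacher, a timetable and a start date, and Study Intervention leaves the frequency of the videos to the teacher. Their changes may therefore move together. Classroom, school type and start order also coincide, so two classrooms cannot separate them.

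At stake is how the secondary results are read. A student-level interval would make a two-classroom, before-and-after comparison look like a precise effect estimate. The abstract says that the results will inform the design of the main trial. A planner who accepts the stated reason might also conclude that measuring more students per class would solve the problem.

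**Working it through.** **Inputs from the article.** Clusters: 2 (Study Design). Clusters per start time: 1 (abstract, Participants). Students measured per class: m = 20 planned (Sample Size), m = 10 with baseline data at submission (Results). Nominal level: 95% (abstract). Sample Size states that no calculation was done and no expected interval width is given, so there is no figure to reproduce.

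**Assumptions.** Stable differences between classrooms cancel in a within-student change. The relevant ICC, ρ, is therefore the share of the variance of the *change* that lies between classrooms. The article gives none; ρ is taken from 0 to 0.20. The interval is taken to be computed over all measured students, ignoring classroom.

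**Step 1: width.** Design effect DE = 1 + (m − 1)ρ. The standard error is understated by a factor of √DE. Approximate coverage is 2Φ(1.96/√DE) − 1. Example, m = 20 and ρ = 0.05: DE = 1 + 19 × 0.05 = 1.95, √DE = 1.40, 1.96/1.40 = 1.40, coverage 84%. A simulation (200,000 runs per cell, student-level t interval on 2m − 1 df) checks the formula.

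| m | ρ | DE | √DE | Coverage, formula | Coverage, simulated |
|---|---|---|---|---|---|
| 20 | 0 | 1.00 | 1.00 | 95.0% | 95.0% |
| 20 | 0.01 | 1.19 | 1.09 | 92.8% | 92.7% |
| 20 | 0.05 | 1.95 | 1.40 | 84.0% | 83.9% |
| 20 | 0.10 | 2.90 | 1.70 | 75.0% | 74.6% |
| 20 | 0.20 | 4.80 | 2.19 | 62.9% | 61.3% |
| 10 | 0 | 1.00 | 1.00 | 95.0% | 95.0% |
| 10 | 0.01 | 1.09 | 1.04 | 94.0% | 93.9% |
| 10 | 0.05 | 1.45 | 1.20 | 89.6% | 89.7% |
| 10 | 0.10 | 1.90 | 1.38 | 84.5% | 84.5% |
| 10 | 0.20 | 2.80 | 1.67 | 75.9% | 74.8% |

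At any ρ above 0, coverage is worse with 20 students per class than with 10. More students per class do not repair the interval.

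**Step 2: using the classroom as the unit.** Two classroom mean changes leave 2 − 1 = 1 df. The t multiplier is 12.71, against 2.02 (39 df, m = 20) or 2.09 (19 df, m = 10) at student level. Median simulated half-widths at ρ = 0.05, in SDs of change:
- m = 20: 1.89 against 0.313, a ratio of 6.0.
- m = 10: 2.31 against 0.454, a ratio of 5.1.

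This interval has its nominal coverage when there is no time effect, but it is too wide to inform anything.

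**Step 3: time.** With a baseline and an end measurement per student, the intervention period always comes second. Any shift over time is added to the estimated effect. Estimating one time parameter as well as the effect from two classroom changes leaves 2 − 2 = 0 df. If both classrooms have the same interval between measurements, the two parameters cannot be separated at all.

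Simulated coverage at ρ = 0 under an assumed time shift common to both classes:
- 0.1 SD of change: 90.6% (m = 20) and 92.9% (m = 10).
- 0.2 SD: 76.5% and 86.3%.
- 0.5 SD: 13.0% and 43.6%.

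This failure does not depend on the ICC, and adjusting the width for clustering does not cure it.

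**The case against.** The article does not say how the interval will be computed. It could be a paired interval within each classroom, which fits each classroom being its own control and would be unobjectionable if labelled as such. A condensed article may leave that detail to a fuller document. The ICC of change could be close to 0, and then the width is about right. The abstract calls the estimates preliminary, the effects are a secondary objective, and none of the six feasibility criteria uses an interval; the activPAL criterion is a 15% reduction in sitting time.

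Most of this stands, and it limits the point. Several stronger readings are tempting but not supported:
- A flat contradiction. The Statistical Analysis sentence is hedged and opens from the feasibility outcomes, so this is an unresolved inconsistency.
- That the abstract names the student as unit of analysis. Only Trial Design does; the abstract gives the unit of randomization.
- That the interval is certainly too narrow. That needs a student-level calculation ignoring classroom and an ICC of change above 0.
- That 10 per class is the final sample. It is the number with baseline data at submission; 20 are planned.
- That the interval will be used to size the main trial. No section says so.

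The defence does not remove the mismatch between two affirmative statements, the student named as unit of analysis with only two randomized clusters, or the confounding with time.

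**Conclusion.** The concern holds in conditional form. The abstract and the Statistical Analysis section need reconciling whatever method is intended. If the interval is computed over students ignoring classroom, it is not a valid interval for the intervention effect.

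Over the assumed ICC range of 0 to 0.20, coverage of a nominal 95% interval runs from 95% down to 61-63% with 20 students per class, and from 95% down to 75-76% with 10. Confounding with time is additional and remains at an ICC of 0. A classroom-level interval on 1 df is no practical alternative. The stated reason for avoiding inference is incomplete, because the limit is two clusters and not only the number of students.

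Severity is moderate: the effects are a secondary, preliminary aim and progression does not depend on the interval. The timing argument rests on the two measurement occasions described in Participants; Figure 1 and the appendix were not available for this check.

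**What to change.** Make the abstract, Trial Design and Statistical Analysis agree:
- Remove the pooled 95% CI for the intervention effect.
- For each classroom, report n, the mean paired change and the SD of change, with the two classrooms side by side.
- Label any interval as within-class sampling error, conditional on that classroom.
- State that the number of clusters, and not only the number of students, rules out inference, and that between-classroom variation cannot be estimated from two classrooms.
- State that the before-and-after change cannot be separated from time and should not serve as the effect size for the main trial.

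The cost is a change of wording, with no new data or measurements. The reported precision will look less favourable.

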**Results:**

At the time of submission, two classrooms have been recruited into the study. Baseline physical activity and postural dynamism data have been collected from 10 participants from each class.

**Conclusions:**

The results of this feasibility stepped-wedge cluster randomized controlled trial will be useful in informing the design of the main trial to assess whether this multifaceted intervention of multifunctional classroom furniture that allows for sitting and standing as well as a video-based curriculum versus usual care has any effect on sedentary behavior in low-resource-setting primary schools.

**Trial Registration:**

Pan African Trials Registry PACTR201811799476016; https://tinyurl.com/y4upoys8

**International Registered Report Identifier (IRRID):**

RR1-10.2196/18522

## Introduction

### Background

A lifestyle of sedentary behavior may result in the development of noncommunicable conditions such as metabolic syndrome [1] and poor back health [2]. Metabolic syndrome represents a range of interrelated disorders comprising abdominal obesity, raised blood pressure, dyslipidemia, and hyperglycemia [1]. Even when the guidelines for physical activity are met, sedentariness remains an independent risk factor for the development of noncommunicable diseases (NCDs) [3].

The school environment typically requires students to remain seated for prolonged periods of time, thus encouraging sedentary behavior [4]. Prolonged periods of sitting with accentuated thoracic kyphosis reduces and even reverses the natural, protective spinal curvature [5]. Although the etiology of back pain is multifactorial, poor postural alignment and reduced postural dynamism (number and extent of body movements while sitting) are common risk factors of back pain [6-9]. Static sitting may place an excessive physiological load on the spinal structures, leading to accumulative microdamage and consequent pain [10]. Dynamic posture reduces the accumulated damage from prolonged periods of sitting by breaking up the sitting periods into smaller epochs, which may help to reduce back pain [11] owing to a reduction in accumulated intervertebral disc compression [12]. Therefore, modifying the design of school furniture to optimize postural alignment and dynamism during sitting and increasing sit-stand transitions may address the potential health risks caused by prolonged sitting in the school environment. However, most of the research aimed at testing the efficacy of dynamic classroom furniture to increase classroom physical activity has been conducted in high-income settings [11,13-24]. Moreover, there is a paucity of studies regarding the effectiveness of classroom furniture in reducing classroom sedentariness and promoting back health, especially for low-to-middle income countries (LMICs). Currently, no back health intervention studies have examined an association with sedentary behavior, despite its recognition as an important risk factor. Furthermore, the majority of studies have implemented unimodal interventions to address either back pain or NCDs separately. Designing health programs that address more than one health problem is preferable in LMICs where health budgets are constrained. To our knowledge, no studies have addressed sedentariness by assessing the effect of a multimodal approach aimed at reducing sedentariness and promoting back health.

Prior to embarking on a large, definitive trial to assess a multimodal intervention aimed at reducing classroom sedentariness, an imperative first step is conducting a feasibility study [25]. Feasibility studies provide information on whether an intervention is contextually viable [26]. Therefore, the primary aim of this project is to assess the feasibility of conducting a multimodal, contextualized classroom-based intervention aimed at reducing sedentariness in primary school students. The secondary project aim is to yield preliminary data on the effect of the intervention on physiological outcomes of interest, namely physical activity and postural dynamism.

### Study Aims and Objectives

#### Primary Objectives

Adherence and project pragmatics are the two primary feasibility outcomes of interest in this study. Adherence to the intervention refers to the extent to which students and teachers comply with the novel furniture and utilize the health education video curriculum. The pragmatics refer to effectively capturing physical activity and postural dynamism data with activPAL microsensors (PAL Technologies, Glasgow, UK) and Noraxon Myomotion (Noraxon, Scottsdale, USA) inertial measurement units (IMUs), respectively. Several pragmatic factors have been identified that could threaten data loss, such as electromagnetic interference from classroom furniture and building infrastructure, Wi-Fi frequency traffic from wireless-enabled devices in close proximity, and IMU sensor battery performance during multiple days of capturing prolonged trials in excess of 1 hour. To our knowledge, activPAL sensors have not previously been used to measure physical activity in this population in South Africa. This study therefore provides the first opportunity to appraise acceptability of using this technology.

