### Study Intervention

The proposed intervention has two components: (1) novel height-adjustable sit-stand desks (KUZE desks; patent reference: A2017/01821), and (2) a series of health educational videos that encourage reduced classroom sedentariness and promote classroom physical activity. Usual classroom furniture will be replaced with KUZE desks after baseline measurements are performed. Prior to the implementation of the intervention, the researcher will train the students and teachers on how to safely and effectively use the KUZE desks. The training will include how to select and adjust the seat and desk height for sitting and standing. When used as a standing desk, the KUZE desk is placed on the existing desk and adjusted to the appropriate height.

During a teacher consultation prior to the onset of the project, the teacher will be shown the playlist of short health education videos provided on a mobile external hard drive. The videos are voiceover animations about the importance of reducing classroom sedentariness, awareness of good sitting posture, and increasing physical activity beyond the classroom. All videos contain an interactive segment of physical activity linked with simple mathematics tasks that the students are encouraged to engage with. The frequency at which the videos should be played will not be prescribed to the teacher. Strategies based on findings from a prior qualitative process that explored the potential barriers and facilitators to implementing a classroom-based intervention in primary school classes will be discussed.

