### Feasibility Outcomes

Two broad feasibility criteria categories are to be considered: adherence and project pragmatics. The detailed success criteria and indicators are outlined in Table 1.

**Table 1 table1:** Feasibility criteria.

Feasibility criteria	Success indicator	Measurement method
Delivery of the health education videos	The teacher develops a suitable routine of playing the videos and adheres to it	Qualitative feedback at exit interview (at 13weeks)
Acceptance of KUZE as a sit-stand desk	Students and teachers accepted the KUZE as the classroom furniture for the entire study period	Qualitative feedback at exit interview (at 13 weeks)
Compliance with wearing activPAL and IMU^a^ sensors	100% of the subsample selected to be monitored agreed and complied to wearing the sensors during the data collection sessions	Researcher monitoring dropout rate
Usage of the KUZE desk	15% reduction in sitting time, reduction in episodes of prolonged sitting, increase in standing time, increase in sit-to-stand transitions	activPAL
Classroom retention to the study	All classrooms initially recruited remain in the study	Researcher monitoring
Integrity of physical activity and postural dynamism data	The integrity (degree of corrupt data due to technical or human factors) of 80% of all data captured with objective tools	Researcher monitoring

^a^IMU: inertial measurement unit.

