### Physiological Measures

Classroom sitting will be measured with activPAL3 microsensors attached to the anterior right thigh as prescribed by the user manual. The outcomes of interest will include total classroom sitting time, standing time, and sit-to-stand transitions. The activPAL3 microsensor will be placed on the participants prior to the start of the school day and removed at the end of the school day before they are dismissed home. The data captured during recess times will be excluded from the data analysis. The activPAL3 microsensor has been increasingly used to objectively measure physical activity in recent years owing to its user-friendliness, practicality, and validity [30].

Postural dynamism will be measured using Noraxon Myomotion IMUs, which combine triaxial gyroscopes, accelerometers, and magnetometers. IMUs placed on the head, neck, thorax, and sacrum will be able to produce 3D kinematic and temporal outcomes, which can then be processed to produce a postural dynamism outcome.

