### Sample Size

A sample size calculation was not performed as per the CONSORT extension statement for feasibility studies [25]. A classroom from a fee-paying and a nonfee-paying school will be recruited. The diversity within the sample is expected to provide a sufficiently broad spectrum of considerations to assess the feasibility of the intervention and the pragmatics of data collection. To limit the impact on the classroom environment, no more than 10 morning data collection sessions per cluster are planned. The availability of only 2 Noraxon systems and 10 activPAL sensors presents a logistical constraint that will only allow for the collection of postural dynamism data and classroom physical activity data from 20 students from each cluster respectively. The sample selected for measuring physiological outcomes will be randomly chosen from the class list. An equal number of males and females of 10 to 11-year-old students will be sampled. The participants in the qualitative study will include students who took part in physiological data collection and those who were only exposed to the intervention but did not provide physiological data.

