### Physiological Outcomes

Measurements will be taken from the study sample from each classroom at baseline and after implementation of the intervention to assess its effect. Classroom sitting will be measured for 10 consecutive school days using the activPAL3 microsensor. The sensor will be wrapped in a waterproof nitrile sleeve and attached to the proximal anterior right thigh of the participant with Hydrofilm. Participants will be required to wear the sensor from the beginning of the school day and it will be removed and collected by the researcher by the end of the school day.

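### The single 80% integrity criterion pools usual-furniture and KUZE-desk recordings, so a shortfall at the new desks can be offset by good baseline data

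*Protocol article*

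**What the plan says.** Under Primary Objectives, the protocol article makes effective capture of activPAL and IMU data the pragmatics half of its primary feasibility outcome. Its list of threats to that capture includes "electromagnetic interference from classroom furniture and building infrastructure, Wi-Fi frequency traffic from wireless-enabled devices in close proximity".

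Study Intervention states: "Usual classroom furniture will be replaced with KUZE desks after baseline measurements are performed". For standing use, the same section adds: "When used as a standing desk, the KUZE desk is placed on the existing desk and adjusted to the appropriate height". Physiological Outcomes fixes two measurement phases: "Measurements will be taken from the study sample from each classroom at baseline and after implementation of the intervention to assess its effect".

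The criterion for data capture is the last row of Table 1 (Feasibility Outcomes): "The integrity (degree of corrupt data due to technical or human factors) of 80% of all data captured with objective tools". The method is monitoring by the researcher. No threshold is given by phase. The only breakdown of feasibility reporting stated under Statistical Analysis is acceptability by cluster and overall.

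Under Interpretation of Feasibility Success Criteria, integrity is one of six criteria, and all six must be met to continue without modification.

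**The concern.** The protocol names furniture as a possible source of interference, and furniture is what the intervention changes. Phase and furniture are aligned: baseline is recorded at the usual furniture, follow-up after the KUZE desks have come in. If furniture affects capture at all, integrity could differ between the phases.

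A single percentage over all captured data averages that difference away. A main trial of this intervention would have to record children at the KUZE desks, so integrity in that phase bears most directly on whether it can be done. A pass carried by baseline recordings would not show it. The criterion could be counted as met, and the study could move on without changing its measurement procedure, when capture at the new desks had fallen short of the protocol's own 80%.

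**Working it through.** **The plan's figure.** The 80% is a chosen threshold without a derivation, so there is nothing to reproduce. I read it as at least 80% of captured data being intact. The check is how low integrity in the KUZE phase can go while the pooled figure still reaches 80%.

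**Inputs from the protocol.** Threshold 80% of all data captured (Table 1). Two phases (Physiological Outcomes). Planned measured sample of 20 students per cluster (Sample Size) in two clusters, hence 20 × 2 = 40.

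**Assumptions, not in the protocol.** The integrity rates in each phase; the share *w* of all data that comes from baseline (0.5, varied from 0.4 to 0.6); and, for the last step, one independent record per student per phase.

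**Step 1: pooled integrity.** With *b* the intact proportion at baseline and *k* that at the KUZE desks,

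pooled = *w*·*b* + (1 − *w*)·*k*.

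With *w* = 0.5, *b* = 95% and *k* = 65%: (95 + 65)/2 = 80%, a pass, although the KUZE phase is 15 points below the threshold.

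**Step 2: lowest passing KUZE-phase integrity.** Setting pooled = 80% gives *k* = (0.80 − *w*·*b*)/(1 − *w*).

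| Baseline share *w* | *b* = 100% | *b* = 95% | *b* = 90% | *b* = 85% |
|---|---|---|---|---|
| 0.4 | 66.7% | 70.0% | 73.3% | 76.7% |
| 0.5 | 60.0% | 65.0% | 70.0% | 75.0% |
| 0.6 | 50.0% | 57.5% | 65.0% | 72.5% |

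The formula is symmetric: with *w* = 0.5, a baseline phase at 60% also passes if the KUZE phase is at 100%.

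**Step 3: in counts.** With 40 records per phase, the pooled rule needs 0.80 × 80 = 64 intact. If baseline gives 40, 38 or 36 intact, the KUZE phase needs only 24 (60%), 26 (65%) or 28 (70%) of 40. A rule applied to each phase needs 0.80 × 40 = 32 of 40.

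**Step 4: chance of passing.** Taking the two phases as independent binomials of 40 records each:

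| True integrity, baseline / KUZE | Pooled rule (at least 64 of 80) | KUZE phase alone (at least 32 of 40) |
|---|---|---|
| 95% / 65% | 57% | 3% |
| 95% / 70% | 79% | 11% |

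Under these assumed rates, the pooled rule would usually pass a KUZE phase whose true integrity is below 80%.

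**The case against.** The strongest reply is that the protocol gives no sign that the KUZE desks are the problem. It speaks of classroom furniture in general, and the usual desks are classroom furniture too. Neither the KUZE desk's material nor its interference relative to the usual desk is stated, and in standing use the existing desk stays underneath. Interference may rise, fall or stay the same. This stands, and it rules out several stronger readings.

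- *A reader might infer that the risk is not monitored once the new desks are in.* That is wrong. Measurements are taken after implementation, and the criterion covers all captured data. What is missing is a threshold for each phase.
- *A reader might infer that the risk arises with the new desks.* The documents support only that exposure may change, in either direction.
- *A reader might infer that a before-after change in postural dynamism would be sensor distortion.* Physiological Measures does describe "Noraxon Myomotion IMUs, which combine triaxial gyroscopes, accelerometers, and magnetometers", but Primary Objectives speaks of data loss, not of biased readings. Distortion that nobody recognised would also leave the integrity percentage untouched, so splitting that percentage would not reveal it. Nor is there a basis for asking for a reanalysis without the magnetometer: the article does not say what the device or software allows, and the method for analysing postural data is itself still to be developed.

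The other replies have some force. The phase rates are hypothetical, and any pooled percentage can hide a subgroup. Phase deserves singling out because the protocol itself names furniture as a threat and changes it between phases. The effect on the decision is bounded: if integrity alone failed, five of six criteria would still be met and the result would be minor modifications rather than an unmodified continuation. Finally, a descriptive breakdown by phase could well be left to a fuller document. The point here, however, concerns the pass rule, which the article does state, in Table 1.

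**Conclusion.** The concern holds in a limited form. Table 1's integrity criterion can be met while capture at the KUZE desks falls short of 80%, because the other phase can make up the difference. With equal data volumes, the KUZE phase can be as low as 60% to 75% when baseline is 100% to 85%; with a baseline share of 40% to 60%, the full range is 50% to 76.7%. These figures show what the rule permits. They do not predict what will happen, since the documents give no integrity rate for either phase.

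The consequence is that the progression rule could count data capture as feasible without having shown it at the desks the main trial would use. This is worth correcting because it touches a primary feasibility outcome and is cheap to mend. It does not invalidate the study. The conclusion rests on reading a single threshold on all captured data as pooled over phases. The article does not say so in those words, but nothing in it points to scoring by phase.

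**What to change.** In the last row of Table 1, score integrity separately for the baseline phase (usual furniture) and the KUZE-desk phase, and count the criterion as met only if at least 80% of the data are intact in each. Report both figures beside any before-after result for postural dynamism, so that the reader can see whether data quality differed between the phases being compared.

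This is one change of wording and a simple split of data already to be collected. The price is a somewhat harder criterion: each phase must pass on its own, with fewer records behind each percentage, so a chance shortfall in either phase can fail it.
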